## **5. SELECTION OF TRIAL SUBJECTS**

### **5.1 Recruitment**

The study patients will be recruited among the affected children in the neurologic clinic of the UKBB as well as using the Swiss and German DMD Register. Currently approximately 120 DMD patients are registered in the Swiss Register. To find the patients the Swiss DMD Register will be searched in alphabetic, systematic order for inclusion and exclusion criteria and matching patients will be contacted and informed about the study. Furthermore, an advertisement will be placed on the website Swiss and German DMD Register after approval of the Ethics Committee and Swissmedic.

Healthy volunteers will be recruited from our hospital. Children and their caregivers having a routine blood drawing prior to an elective surgical procedure will be asked if they are willing to give an additional amount of blood for this study.

### **5.2 Inclusion criteria**

- Molecular diagnosis of DMD

- Patients 6.5 - 10 years of age at time of screening
- Ambulant
- Ability to walk 150 m in the 6 min walking distance (6MWT)
- D1 subdomain of the MFM scale >40%
- stable treatment with steroids for >6 months or steroid naïve patients

### **5.3 Exclusion criteria**

- Previous (3 months or less) or concomitant participation in any other therapeutic trial
- Use of L-citrulline, L-arginine or metformin within the last 3 months
- Known individual hypersensitivity to L-citrulline or metformin
- known or suspected malignancy
- Other chronic disease or clinical relevant limitation of renal, liver, heart function according to discretion of investigator
- start of cortisone treatment or change in dosage <6 months prior to screening

### **5.4 Inclusion criteria healthy volunteers**

- Male sex
- Aged between 6.5-10 and 18-60 years.

### **5.5 Exclusion criteria healthy volunteers**

- Previous (3 months or less) or concomitant participation in any other therapeutic trial
- Use of L-citrulline, L-arginine or metformin within the last 3 months
- Known genetic or acquired neuromuscular disorder
- known or suspected malignancy
- Other chronic disease or clinical relevant limitation of renal, liver, heart function according to discretion of investigator

## **6. ASSESSMENT OF EFFECTIVENESS**

### **6.1. Effectiveness parameter: measuring methods and time**

- 1) Mean change of MFM D1 subscore from baseline to week 26 under L-citrulline/metformin therapy compared to placebo

- 2) Mean change of MFM total score, the D2, and D3 MFM subscores from baseline to week 26 under L-citrulline/metformin therapy compared to placebo (for details see 1)
- 3) Mean change of walking distance from baseline to week 26 under L-citrulline/metformin therapy compared to placebo assessed with the six-minute walk test (for details see 1)
- 4) Change of quantitative muscle MRI including muscle fat content (MFC) and T2 times of thigh muscles visualized by MRI (Magnetic Resonance Imaging) in both groups at week 26 versus baseline (for details see 2.2.2)
- 5) Change in the plasma / urine concentration for markers of muscle necrosis (resting creatine kinase, plasma), oxidative stress (8OHdG, urine; carbonylated proteins, 4-HNE, serum), nitrosative stress (nitrotyrosin, plasma; ADMA , serum; cGMP, urine), and change of miRNAs serum concentration in both groups at week 26 compared to baseline.
- 6) Normal values for makers of oxidative stress, nitrosative stress and changes of mi-RNA in serum and urine will be obtained in 10-20 healthy male adults aged 18 to 60 years and 10-20 boys aged 6.5 to 10 years.
- 6) Mean change of quantitative muscle force (QMT) of knee extension and elbow flexion using hand held dynamometry (HHD) from baseline to week 26 under L-citrulline/metformin therapy compared to placebo

## **7. SAFETY**

### **7.1 Safety parameter: measuring methods and time**

At every study visit a clinical examination will be performed and the vital parameters blood pressure and heart rate will be measured. The assessment of blood chemistry and of the following parameters is foreseen at every visit (respectively visit 1 or 2):

- full blood count, as with the intake of metformin in the context of the registration trials isolated cases of leucopenia, thrombopenia, and haemolytic anaemia were observed
- clinical chemistry (transaminasis, creatinine, electrolytes, urea),
- marker of the muscle necrosis (creatine kinase concentration),
- makers of oxidative stress: (8OHdG urine concentrations, carbonylated preteins and 4-HNE serum concentration)
- markers of nitrosative stress (nitrotyrosin, plasma; ADMA; serum; cGMP, urine)
- all amino acids
- glucose metabolism marker (HbA1c)
- lipid metabolism marker (cholesterol, HDL, LDL, triglycerides)

The intake of metformin has to be stopped in case of clinically significant changes (increase of creatinine and transaminasis  $>2 \times \text{ULN}$ )

If pathologic changes independent of the known muscle disease should be detected, the affected patients will be informed immediately and the possibilities of further investigation, respectively treatment of these abnormalities according to current medical knowledge will be discussed.

## **7.2 Follow-up observation for trial subjects with adverse reactions**

Patients with adverse reactions which have occurred in the context of the study will be followed up by the investigator up to 30 days after the last visit.

## **8. STATISTICS**

### **8.1 Definition of the primary end point and secondary endpoints**

- 1) Mean change of MFM D1 subscore from baseline to week 26 under L-citrulline/metformin therapy compared to placebo
- 2) Mean change of MFM total score, the D2, and D3 MFM subscores from baseline to week 26 under L-citrulline/metformin therapy compared to placebo

- 3) Mean change of walking distance from baseline to week 26 under L-citrulline/metformin therapy compared to placebo assessed with the six-minute walk test
- 4) Change of quantitative muscle MRI including muscle fat content (MFC) and T2 times of thigh muscles visualized by MRI (Magnetic Resonance Imaging) in both groups at week 26 versus baseline
- 5) Change in the plasma / urine concentration for markers of muscle necrosis (resting creatine kinase, plasma), oxidative stress (8OHdG, urine; carbonylated preteins, 4-HNE serum), nitrosative stress (nitrotyrosin, plasma; ADMA, serum; cGMP, urine), and change of miRNAs serum concentration in both groups at week 26 compared to baseline values and to values of age and sex matched healthy volunteers.
- 6) Mean change of quantitative muscle force (QMT) of knee extension and elbow flexion using hand held dynamometry (HHD) from baseline to week 26 under L-citrulline/metformin therapy compared to placebo

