### 3.1.1 Own pilot study

After having established all necessary assessment tools in Basel we performed a small pilot study to examine if a 16 week treatment with 3 x 2,5 g/d of L-arginine (NO precursor) and 2 x 250 mg/d Metformin (pharmacological AMPK activator) could serve as therapeutic treatment for DMD. All necessary permissions from the local ethical committee and the Swissmedic were obtained before the beginning of the study. A total of five ambulant DMD patients aged between 7-10 years were enrolled and treated in our pilot-study. One patient was treated with corticosteroids (standard treatment of care), while others had refused to take steroids because of possible side effects before they entered the trial. No major side effects were observed. No patient dropped out. In addition to the presented data (see below) we performed muscle biopsies. We are currently analysing the gene expression in muscle tissue of proteins (baseline and after treatment) involved with NO metabolism, reactive oxidative stress, fatty acid oxidation, and mitochondrial biogenesis.

Laboratory testing revealed no significant change in creatine kinase levels, renal and liver function tests, glucose, and HDL / LDL values (baseline vs. posttreatment). DEXA scans revealed that the average whole body muscle content (70,6 % baseline vs. 70,3% posttreatment) and fat content did not change significantly. Indirect calorimetry assessing energy and muscle metabolism in vivo showed important changes. As previously postulated metabolism changed and the relative carbohydrate contribution to the oxidation rate decreased in all patients (mean change -17,9%), while the relative fatty acid contribution to the oxidation rate increased (mean change 13,9%). Quantitative muscle MRI showed that metformin and l-arginine treated patients had an MFC increase of 1,4 % corresponding to an annual increase of 4,4 %. Ambulant DMD patients older than 8 years receiving standard treatment with steroids show a median annual MFC increase of 8-9 % (22). This indicates that L-arginine and metformin may slow the progression of muscle degeneration in DMD.

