
DMD patients aged 4–17 years in the Italian cohort showed that the 6MWD performances increased (approximately 33 m/year) with age up to 7 years, with a clear point of slope change at approximately 7 years. After the age of 7 years, there was a variable decline in the 6MWT (-12 m/year) (24).

Secondary outcome measures:

- 2) Mean change of MFM total score, the D2, and D3 MFM subscores from baseline to week 26 under L-citrulline/metformin therapy compared to placebo (for details see 1)
- 3) Mean change of walking distance from baseline to week 26 under L-citrulline/metformin therapy compared to placebo assessed with the six-minute walk test (for details see 1)
- 4) Change of quantitative muscle MRI including muscle fat content (MFC) and T2 times of thigh muscles visualized by MRI (Magnetic Resonance Imaging) in both groups at week 26 versus baseline (for details see 2.2.2)
- 5) Change in the plasma / urine concentration for markers of muscle necrosis (resting creatine kinase, plasma), oxidative stress (8OHdG, urine; carbonylated proteins, 4-HNE, serum), nitrosative stress (nitrotyrosin, plasma; ADMA, serum; cGMP, urine), and change of miRNAs serum concentration in both groups at week 26 compared to baseline and compared to healthy controls.
- 6) Mean change of quantitative muscle force (QMT) of knee extension and elbow flexion using hand held dynamometry (HHD) from baseline to week 26 under L-citrulline/metformin therapy compared to placebo

Aims of our treatment are a stimulation of NO concentrations (indirect markers nitrotyrosine, ADMA and cGMP), an improvement of the muscular energy situation with reduction of oxidative stress (8OHdG, carbonylated proteins, 4-HNE as markers) and a slowing of the

muscle denegeration (creatine kinase as marker.) Aim of our treatment is a slowing of the natural history of the disease, so we plan to analyse possible serum biomarkers (miRNAs) of disease progression (26).

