## **8.2 Planned number of trial subjects with clearly stated justification (possibly power analysis)**

For sample size estimation the MFM D1 subscore was chosen. Baseline and post-treatment measurements of 5 patients are available from the pilot study. A semi-parametric approach for sample size estimation was chosen that made use of these data. For the 2 min. walking distance, a mean change from baseline to post-treatment of 10 m was expected (estimated from pilot data). For the MFM D1 subscore, a mean change from baseline to post-treatment of 6.1 % was expected (estimated from pilot data). Sample size estimation was repeated for a range of values smaller and larger than the expected mean changes. Further, the influence of two randomisation ratios for the verum/placebo groups, 1:1 and 2:1, on sample size was checked. Each sample size,  $n_i=1, \dots, 40 = 11, \dots, 50$  for the MFM D1 subscore, was evaluated by drawing 99 times an individual data set of size  $n_i$  from the pilot study data set (sampling with replacement). In each of these individual data sets, each patient was randomly assigned to a verum or a placebo group. For each patient, the post-treatment value was

Version 8, 10.09.2015

calculated as the sum of the baseline value and a random variate drawn from a normal distribution with mean and standard deviation estimated from the pilot data. In the case of the placebo group, the mean was set to  $-17.2/54 \times 16$  for the MFM D1 subscore (value taken from Table 2 in (39)). (The values from the literature refer to changes within one year, i.e. 54 weeks, and the pilot study lasted 16 weeks, thus the linear transformation of the values by  $/ 54 \times 16$ .) For the primary endpoint candidate (MFM D1 subscore), assuming a drop-out rate of 10 %, a randomisation ratio of 1:1, and a power of 0.8, c. 42 patients should be recruited in order to be able to analyse 38 complete datasets. Fig. 4 shows how the sample size behaves with regard to the MFM D1 subscore, the power, and the randomisation ratio.

[figure not shown]

Fig. 4. Sample size with regard to the MFM D1 subscore and the power for a randomisation ratio of 1:1. The numbers on the curves indicate the power. The arrow shows how to interpret the plot. The curves are smoothed and only serve illustrative purposes.

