### **8.3 Description of the statistical methods foreseen and the planned intermediate assessments**

Non-parametric Wilcoxon signed rank test

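### The MRI and biomarker secondary endpoints name baseline, not placebo, as comparator; taken literally with the paired test in 8.3, they give within-arm tests that do not estimate a treatment effect

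*Protocol*

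**What the plan says.** Protocol 8.1 lists six endpoints. The primary one reads "Mean change of MFM D1 subscore from baseline to week 26 under L-citrulline/metformin therapy compared to placebo". Items 2 (MFM total, D2, D3), 3 (six-minute walk) and 6 (muscle force) have the same form, with placebo named as comparator.

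Items 4 and 5 are worded differently:
- Item 4 (MFC and T2) is the change of "thigh muscles visualized by MRI (Magnetic Resonance Imaging) in both groups at week 26 versus baseline". Sections 4.1 and 6.1 say the same.
- Item 5 (creatine kinase, oxidative and nitrosative stress markers, miRNAs) is the change "in both groups at week 26 compared to baseline values and to values of age and sex matched healthy volunteers" in 8.1, and "in both groups at week 26 compared to baseline and compared to healthy controls" in 4.1. In 6.1 it stops at baseline; healthy volunteers appear there only in a separate entry on normal values.

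The whole of section 8.3 is "Non-parametric Wilcoxon signed rank test".

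On purpose, section 3.2 says the trial is to confirm the pilot findings under placebo control, including slower fatty degeneration on MRI. The end of 4.1 gives slower muscle degeneration, with creatine kinase as its marker, as a treatment aim. Section 11.3 says the placebo group is needed to demonstrate efficacy.

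**The concern.** The stated aim is relative: less worsening than on placebo. A change from baseline within one arm mixes any drug effect with the natural course of the disease. MFC is expected to rise during the trial, so a significant rise in an arm says little about the drug. The tempting summary, that placebo worsened significantly and active did not, compares two p-values and does not test the difference between arms. The healthy-volunteer comparison in item 5 is not randomised and cannot replace placebo.

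The wording recurs in three sections, so it is not a slip in one place. At stake is whether the imaging and mechanistic results can support the primary endpoint with a randomised comparison.

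**Working it through.** **1. What the protocol's own sample size assumes.** Section 8.2 sizes the trial on MFM D1, "assuming a drop-out rate of 10 %, a randomisation ratio of 1:1, and a power of 0.8", giving 38 complete datasets and about 42 recruited.
- Inputs: active change +6.15 points and SD 11.6 (pilot table in 3.1.1; 8.2 rounds the change to 6.1); placebo change −17.2/54 × 16 = −5.10 (8.2). Two-sided α = 0.05 is assumed, because 8.4 does not state sidedness.
- Difference: 6.15 + 5.10 = 11.25.
- n per arm = 2 × (1.96 + 0.84)² × 11.6² / 11.25² ≈ 16.7, so 17 per arm and 34 in total. Dividing by the rank-test efficiency 0.955 gives 35.6, so 36.
- Simulated at 19 per arm (10,000 runs, normal changes), a rank-sum test on change has power 0.79 and a t-test 0.83.
- Dropout: 38/0.9 = 42.2.

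The stated figure is therefore reproduced to within 2 by a between-arm comparison. The protocol gives no power or sample size for items 4 and 5.

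**2. Expected MFC change without the study drugs.** Section 3.1.1 states: "Ambulant DMD patients older than 8 years receiving standard treatment with steroids show a median annual MFC increase of 8-9" %. Reading this as percentage points and assuming linear progression: 8 × 26/52 = 4.0 and 9 × 26/52 = 4.5; midpoint 4.25.

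**3. No drug effect.** Both arms rise by 4.25 points, 19 per arm (38/2), changes normal, 3,000 runs per setting. The protocol gives no SD of MFC change, so 2 to 10 points is an assumed range. Entries are proportions of trials.

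| Assumed SD | Signed rank significant, active arm | Exactly one arm significant | Placebo arm only | Between-arm rank-sum on change |
|---|---|---|---|---|
| 2 | 1.00 | 0.00 | 0.00 | 0.047 |
| 4 | 0.99 | 0.02 | 0.01 | 0.039 |
| 6 | 0.81 | 0.29 | 0.15 | 0.043 |
| 8 | 0.57 | 0.48 | 0.24 | 0.049 |
| 10 | 0.42 | 0.47 | 0.23 | 0.040 |

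Check on the fourth-to-last results: if each arm is significant with probability p, exactly one is significant with probability 2p(1 − p). For p = 0.81, 0.57 and 0.42 this gives 0.31, 0.49 and 0.49, in line with the simulated 0.29, 0.48 and 0.47. The expression cannot exceed 0.50.

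The assumed rise matters somewhat. At SD 6, exactly one arm is significant in 0.34 of trials for a rise of 4.0 and 0.24 for 4.5.

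**4. Drug works.** Let the active arm progress at the pilot's annualised rate of 4.4% (3.1.1), so 4.4 × 26/52 = 2.2 points, against 4.25 on placebo. The active arm's signed rank test still shows significant change in 0.99 (SD 2), 0.84 (SD 3), 0.61 (SD 4) and 0.30 (SD 6) of trials. The within-arm result can thus report worsening while progression is roughly halved. Between-arm rank-sum power is 0.84, 0.50, 0.32 and 0.16, so the correct contrast is valid but not necessarily well powered.

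For T2 and the item 5 markers the protocol gives no expected course, so no size can be computed. The argument about the comparator is the same.

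**The case against.** A section that defines endpoints may simply name a per-patient variable, change from baseline, and say it is obtained in both arms. Read that way, it does not exclude comparing the arms, and mentioning both groups may even imply it. The trial is randomised and placebo controlled, and MRI and laboratory samples are scheduled at baseline and week 26. A reader might infer from the wording that these endpoints cannot show a treatment effect, or that the randomised comparison has been thrown away. The documents do not support that: the data for the contrast will exist, and the wording is open to the kinder reading.

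The test in 8.3 is also a weak guide to intent. It is one line for all endpoints and fits those that do name placebo no better. The sample-size simulation in 8.2 assigns patients to two arms with different mean changes, so 8.3 may misname the intended test. That is a trial-wide matter, not specific to items 4 and 5. Covariates and transformations may properly be left to a statistical analysis plan.

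The magnitude has limits too. The 8-9% a year is for steroid-treated boys older than 8, not for untreated disease; the trial enrols from 6.5 years and admits steroid-naive boys. A reader might conclude that one-arm-only significance would arise in about half of null trials. That is the top of the range, approached only at SD 8 to 10; at SD 2 to 4 it is 0 to 2%.

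What remains is that items 4 and 5 do state a comparator, and it is baseline, in lists where the other endpoints state placebo. This is more than detail left for later.

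**Conclusion.** The point holds in limited form. Taken literally, items 4 and 5 with the test in 8.3 lead to within-arm tests that do not estimate a treatment effect, contrary to the trial's aim of showing slowing against placebo.

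For MFC with no drug effect, the within-arm test would be significant in about 100% (SD 2) to 42% (SD 10) of trials. Exactly one arm would be significant in about 0% (SD 2), 2% (SD 4), 29% (SD 6) and 47-48% (SD 8-10). A between-arm test stays at about 5%. At small SD the likely failure is that both arms are significant and the result is uninformative; at larger SD it is a misleading split between arms.

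These figures rest on linear progression, on the 8-9% rate carrying over to this population in percentage points, on normal changes, on 19 completers per arm and on the assumed SD range. The conclusion about the comparator depends on none of them. Only secondary endpoints are affected: the definition of the primary endpoint and the data collection stand. The wording should be corrected, but this does not undermine the trial.

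**What to change.** In 4.1, 6.1 and 8.1, redefine items 4 and 5 as the difference between the L-citrulline/metformin and placebo arms in change from baseline to week 26. Test it between arms, for example by a rank-sum test on change or an ANCOVA adjusted for baseline; the choice and any transformation can be left to the analysis plan. Keep within-arm changes and healthy-volunteer comparisons as descriptive, and make the item 5 wording agree across the three sections. Reconcile the test named in 8.3 with every endpoint that is compared with placebo.

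The cost is the rewording of two endpoints in three places and of one line in 8.3. No visits, samples or patients are added.

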## **8.2 Planned number of trial subjects with clearly stated justification (possibly power analysis)**

For sample size estimation the MFM D1 subscore was chosen. Baseline and post-treatment measurements of 5 patients are available from the pilot study. A semi-parametric approach for sample size estimation was chosen that made use of these data. For the 2 min. walking distance, a mean change from baseline to post-treatment of 10 m was expected (estimated from pilot data). For the MFM D1 subscore, a mean change from baseline to post-treatment of 6.1 % was expected (estimated from pilot data). Sample size estimation was repeated for a range of values smaller and larger than the expected mean changes. Further, the influence of two randomisation ratios for the verum/placebo groups, 1:1 and 2:1, on sample size was checked. Each sample size,  $n_i=1, \dots, 40 = 11, \dots, 50$  for the MFM D1 subscore, was evaluated by drawing 99 times an individual data set of size  $n_i$  from the pilot study data set (sampling with replacement). In each of these individual data sets, each patient was randomly assigned to a verum or a placebo group. For each patient, the post-treatment value was

Version 8, 10.09.2015

calculated as the sum of the baseline value and a random variate drawn from a normal distribution with mean and standard deviation estimated from the pilot data. In the case of the placebo group, the mean was set to  $-17.2/54 \times 16$  for the MFM D1 subscore (value taken from Table 2 in (39)). (The values from the literature refer to changes within one year, i.e. 54 weeks, and the pilot study lasted 16 weeks, thus the linear transformation of the values by  $/ 54 \times 16$ .) For the primary endpoint candidate (MFM D1 subscore), assuming a drop-out rate of 10 %, a randomisation ratio of 1:1, and a power of 0.8, c. 42 patients should be recruited in order to be able to analyse 38 complete datasets. Fig. 4 shows how the sample size behaves with regard to the MFM D1 subscore, the power, and the randomisation ratio.

[figure not shown]

Fig. 4. Sample size with regard to the MFM D1 subscore and the power for a randomisation ratio of 1:1. The numbers on the curves indicate the power. The arrow shows how to interpret the plot. The curves are smoothed and only serve illustrative purposes.

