### **3.2 Questionnaire, trial population**

Our aim is to confirm in a double blind placebo controlled trial the observed changes of our own 16 week pilot study in a broader population being treated as postulated by current medical guidelines, including patients under steroid treatment. The precursor study performed on 5 ambulatory DMD patients that showed an improved lipid metabolism, improved functional abilities, prolonged walking distances, and slowing of the rate of progressive fatty degeneration of involved muscle observed on quantitative MRI.

We plan to perform a 26 week placebo controlled RCT (randomized controlled trial) with a total number of 40-50 ambulant DMD patients aged between 6.5 and 10 years. If L-citrulline and metformin are helpful to improve muscle function, a better symptomatic treatment and slowing of muscle degeneration in DMD could be expected, other multicenter trial will be performed.

To obtain normal values for measures of muscle metabolism and mitochondrial function blood and urine samples will be analysed in 10 – 20 healthy age matched male children and 10 – 20 healthy male controls.

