## **4. DESIGN OF THE TRIAL**

### **4.1 Targeted primary endpoint and secondary endpoints**

#### Primary outcome measure

- 1) Mean change of MFM D1 subscore from baseline to week 26 under L-citrulline/metformin therapy compared to placebo

Several tests have been reported in the literature to assess muscle strength and functional ability, to monitor the progression of the disease, and to evaluate the results of drug interventions and rehabilitation. However, most instruments involve only ambulant patients, making adjustments and/or additional assessments necessary when the disease progresses. The MFM, a validated assessment tool to measure motor function in both ambulant and non-ambulant patients with neuromuscular disorders, was developed in 2005 in France. It includes 32 items that evaluate three dimensions of motor performance, including specific motor functions, such as transfers and standing posture (D1), proximal and axial (D2), distal (D3) and a total MFM score involving all of the motor dimensions. The items are scored and summed to comprise a total score, in which the maximum represents normal motor function. The instruction manual, validation examinations and other publications using the MFM can be downloaded at the MFM website (27). In a recent work in DMD, the annual decrease of the total score was 5.8% for the whole group of DMD patients, indicating an overall decline in motor capacities. However, examination of the D1, D2, and D3 subscores independently provided more information depending on the stage of the disease. Indeed, in ambulant patients with DMD, D1 was the most informative dimension, with a mean decrease of 17.2% per year before loss of ambulation in patients aged 6 years and over. After loss of ambulation, D2 became the most informative and showed an average decrease of 9.4% per year. In patients over 14 years, the average decrease in D3 was 10.8% per year (23). D1 seems to us to be particularly interesting because it is related to loss of ambulation and is responsive to short-term changes (3 months) and should provide sufficient information in a 6 months trial. Furthermore, in our own 16 week L-arginine and metformin pilot trial (see below 2.2.4) in ambulant DMD patients the D1 subscore showed the best effect size of all evaluated clinical parameters. Timed clinical functional assessments included the 2 min walking distance in meter (2MWD). In addition to the MFM timed clinical functional assessments (as the 6 min or 2 min walking distance in meter (6MWD /2MWD)) are helpful to assess the muscle function in children with DMD. Due to the progressive nature of DMD MFM values and 2MWD over time until free ambulation is lost (mean progression can be calculated based on data from the literature and correspond to predicted values) (24,25). The 6MWD is also a validated tool to measure the distance an individual is able to walk over a total of six minutes on a hard, flat surface. The goal for the individual is to walk as far as possible in six minutes. The individual is allowed to self-pace and rest as needed as they traverse back and forth along a marked walkway. Data from 112

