## 4.2 Trial design

This is a randomised placebo controlled trial. We plan to enrol 40-50 ambulant DMD patients aged between 6.5 and 10 years. All actively treated patients will get a daily dose of L-citrulline of 7.5 g/d separated in three doses per day (3x 2.5 g) as well as metformin 250 mg three times a day (750 mg daily). The patients randomized to the placebo group will receive matching placebo (sachets and powder and capsule look like verum but do not contain active ingredient). Treatment is given for the period of 26 weeks. Co-medication with glucocorticoids (standard treatment of care) is allowed. At baseline as well as at the end of the study clinical measures, laboratory, and MRI measures will be performed. This includes the MFM scale; 6MWT, MFC assessment using quantitative thigh muscle MRI, and laboratory blood analysis.

[figure not shown]

Figure 3: Flow chart showing the study design with screening, randomisation, and treatment period.

|                                                                                                                                                                                    | Visit 1               | Visit 2              | Visit 3            | Visit 4                              |
|------------------------------------------------------------------------------------------------------------------------------------------------------------------------------------|-----------------------|----------------------|--------------------|--------------------------------------|
|                                                                                                                                                                                    | Screening
(Day -1) | Baseline
(week 0) | Week 13
±7 days | End of Study
(week 26)
±7 days |
| Patient Information/Informed Consent                                                                                                                                               | x                     |                      |                    |                                      |
| Inclusion/Exclusion                                                                                                                                                                | x                     | x                    |                    |                                      |

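### Section 8.2 computes its power of 0.8 for a 16-week change (with a 54-week year), but the primary endpoint is the change at week 26; the figure needs restating, not the sample size

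*Protocol*

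**What the plan says.** The primary endpoint (protocol, section 8.1; the same in 4.1 and 6.1) is "Mean change of MFM D1 subscore from baseline to week 26 under L-citrulline/metformin therapy compared to placebo". Section 4.2 matches it: "Treatment is given for the period of 26 weeks".

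Section 8.2 builds the power calculation from three inputs:

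- **Active-arm mean.** "For the MFM D1 subscore, a mean change from baseline to post-treatment of 6.1 % was expected (estimated from pilot data"). Section 3.1.1 gives the length of that pilot: "we performed a small pilot study to examine if a 16 week treatment with" L-arginine and metformin.
- **SD.** It is also estimated from the pilot and used in both arms; only the mean is reset for placebo. The table of pilot changes in section 3.1.1 gives 11.6 for D1, from five patients.
- **Placebo mean.** It is -17.2/54 × 16. The annual figure matches section 4.1, which describes D1 "with a mean decrease of 17.2% per year before loss of ambulation in patients aged 6 years and over". The reason given for the scaling is that "The values from the literature refer to changes within one year, i.e. 54 weeks, and the pilot study lasted 16 weeks".

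With 1:1 allocation, power 0.8 and 10% drop-out, the section arrives at 38 complete datasets and about 42 recruited. It adds that the estimation was repeated for smaller and larger mean changes.

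**The concern.** Nothing in section 8.2 refers to week 26. The means and the SD describe a 16-week change, while the trial treats and measures for 26 weeks. The stated power of 0.8 is therefore the power of a 16-week trial. The placebo scaling also takes a year as 54 weeks, which is wrong.

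This is the protocol's only power statement for the primary endpoint. A reader cannot tell from it what active-arm change at week 26 the sponsor expects, how variable D1 change is assumed to be by then, or what power 38 datasets give for the comparison that will be made.

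**Working it through.** **Inputs.** Active mean +6.1, SD 11.6 and annual decline 17.2 are from the protocol (sections 8.2, 3.1.1 and 4.1). Alpha is 0.05 (section 8.4), taken as two-sided because sidedness is not stated. A Wilcoxon rank-sum test is assumed for the comparison of two independent groups. There are 19 complete datasets per arm (38 in total). Power is by simulation of normally distributed changes, with at least 20,000 runs per scenario.

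**Step 1: reproduce the stated figure.**

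- Placebo mean: -17.2/54 × 16 = -5.10.
- Difference: 6.1 + 5.10 = 11.20.
- Rank-sum power at SD 11.6, 19 per arm: 0.80 (0.796).
- Recruitment: 38/0.9 = 42.2, in line with about 42.

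The figure reproduces with 16-week inputs. The plan's own 99 draws per sample size carry a Monte Carlo standard error of √(0.8 × 0.2/99) = 0.04, so close agreement is all that can be expected.

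**Step 2: the length of the year.** With 52 weeks, the 16-week placebo mean is -17.2/52 × 16 = -5.29 and the difference is 11.39. Power moves from 0.80 to 0.81. The 54-week year is a plain slip with almost no effect; 16 versus 26 weeks is the substance.

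**Step 3: move the placebo arm to week 26 on the plan's own linear rule.**

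- Placebo mean: -17.2/52 × 26 = -8.60.
- Difference if the +6.1 gain is sustained: 6.1 + 8.60 = 14.70.

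**Step 4: power of 38 complete datasets at week 26.** The protocol gives no week-26 active change and no week-26 SD, so both are assumptions. An SD growing with the square root of time would be 11.6 × √(26/16) = 14.8.

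| Scenario | Difference | SD | Rank-sum power |
|---|---|---|---|
| Plan as written (16 weeks) | 11.20 | 11.6 | 0.80 |
| Week 26, +6.1 sustained | 14.70 | 11.6 | 0.96 |
| Week 26, +6.1 sustained, larger SD | 14.70 | 14.8 | 0.82 |
| Week 26, difference kept at 11.2, larger SD | 11.20 | 14.8 | 0.58 |

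**Step 5: a separate effect assumption.** If the active arm is merely stable (0 versus -8.6, SD 11.6), power is 0.57. This figure comes from replacing the active mean of +6.1 with 0, not from the time error. The same replacement at 16 weeks (0 versus -5.1) gives 0.24, so moving to week 26 raises the power for that scenario.

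**The case against.** The strongest reply is that the mismatch does no harm. With only the time scaling corrected, power rises from 0.80 to about 0.96. Even with the SD inflated to 14.8, a sustained gain still gives about 0.82. About 42 patients is therefore not shown to be too few. That stands, and it sets the severity. It does not make 0.8 the right figure for week 26, and no section presents the 16-week difference as a deliberate cautious choice.

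A second reply is that section 8.2 repeated the estimation over a range of mean changes and plots the result in its Figure 4, which is not visible in the text at hand. That partly covers other effect sizes. However, the only placebo mean described is the 16-week one, and the stated 38 and 42 are not tied to any week-26 scenario.

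A reader might also draw three stronger conclusions that the protocol does not support:

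- **That the trial is underpowered because of this error.** Power falls below 0.8 only under further assumptions about the SD or the active change, as in the last row of the table and in step 5.
- **That powering on a gain contradicts the aim.** Section 4.1 does say "Aim of our treatment is a slowing of the natural history of the disease", but that sentence introduces the serum biomarkers. Section 3.2 sets out to confirm the changes seen in the pilot, and section 3.3 hypothesises improved strength. A gain estimated from five patients may be optimistic, but that is a different criticism.
- **That the enrolment range is inconsistent.** Section 3.2 plans a "total number of 40-50 ambulant DMD patients aged between 6.5 and 10 years". That range contains the approximate target of 42. At 40 enrolled, 36 would be complete (40 × 0.9), with power of about 0.78 on the 16-week inputs, which is within the simulation's own error.

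**Conclusion.** The point holds as a wrong stated figure. The power of 0.8 with 38 complete datasets belongs to a 16-week difference of 11.2, not to the week-26 endpoint. On the plan's own linear decline, with the pilot gain sustained and the pilot SD unchanged, power at week 26 is about 0.96, so the time error taken alone is conservative. With an SD of 14.8 it is about 0.82, or about 0.58 if the difference also stays at 11.2. These values rest on a two-sided 0.05 rank-sum test, 19 per arm and normally distributed changes. The week-26 active change and the larger SD are assumptions, because the protocol states neither. This should be fixed, but it gives no ground for changing the sample size.

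**What to change.** In section 8.2:

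- Replace the factor /54 × 16 with /52 × 26, which gives a placebo change of -8.6.
- State the active-arm change and the SD assumed at week 26, with the reason for each.
- Restate the power of 38 complete datasets under those assumptions, with a short sensitivity range such as the week-26 rows of the table above.
- If a halted-decline scenario (0 versus -8.6) is shown, label it as a separate effect assumption.

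Alternatively, keep the 11.2-point difference and say explicitly, with a justification, that it is a deliberate choice for week 26.

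The cost is one rerun of an existing simulation and a few lines of text. The target of about 42 and the range of 40 to 50 can stay as they are.
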